**Methods:**

This randomized controlled trial will evaluate the efficacy of a behaviorally focused, family-centered intervention, the MySmileBuddy Program (MSB Program), to reduce ECC progression in high-risk preschoolers in New York City. Recruitment will target 858 children ages 24–71 months with ECC and their parents from primary care medical and dental clinics. The study aims to assess the MSB Program’s efficacy to: (1) decrease ECC progression measured 12-months post-randomization; and (2) enhance adoption of a low cariogenic diet and twice-daily fluoridated toothpaste use compared to control group. Potential causal pathways (mediators and moderators) will be explored. The MSB Program equips community health workers (CHWs) with an app that facilitates multilevel risk assessment and provides motivational interviewing-based counseling to inform parents about the caries process, develop personalized goals, and create family-level action plans to achieve targeted behaviors. Social support from CHWs (4 interactions during the 6-month intervention, supplemented by up to 4 in-person/remote contacts throughout the 12-month study period, based on need) is bolstered by automated text messages. Participants will be randomized to a Control Group (paper-based educational handout plus toothbrushes and fluoridated toothpaste for the child) or Intervention Group (MSB Program, two tooth-brushing observations with feedback and instruction, and toothbrushes and toothpaste for the entire family). All children will receive visual ICDAS dental examinations and parents will complete study measures at baseline and 12-months. An incentive up to $150 plus round-trip transit cards ($5.50 value) will be provided.

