### Explanatory objective (secondary 2)

To assess causal pathways (i.e., mediators and moderators) through which the MSB Program influences twice-daily fluoridated toothpaste use and consumption of a low cariogenic diet. We hypothesize that the MSB Program will influence motivation, the ability to act on motivation, and support to maintain oral hygiene and dietary behaviors which may be conditioned by demographic, social, and contextual factors.

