### Enrollment

At the CCPH screening visit, all parents will be given a gift card valued at $20.00, provided a written report of screening findings, and offered a written referral for routine follow-up dental care along with a printed list of area dentists who treat young children. Parents of children confirmed to have ECC will be invited to participate in the study, asked to provide written informed consent, and informed that they will be randomized to a Control or Intervention Group. Parents who enroll in the study will complete an interview with a CHW, which includes administration of the pre-intervention survey instrument. Their children will receive a visual oral examination with tooth surface-specific charting of caries experience at this baseline visit (T1). Parents will confirm agreement to attend a follow up visit at 12 months (T2) when they will again participate in a CHW interview and survey and their children will have a second study-specific dental examination and charting. Enrolled parents who meet these requirements will be given an additional $30.00 participation incentive. Randomization will be stratified by age (24-48 and 49-71 months) and recruitment site, with approximately equal numbers in each Group using a biased-coin design facilitated by computerized randomization software. Oral examinations will be performed in a consistent manner by one of two study dental examiners blinded to Group assignment.

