### Control group

At T1, parents in the Control Group will complete the same baseline interview and survey as parents in the Intervention Group but will not engage in the MSB Program. Rather than receiving MSB Program-specific educational materials, they will receive materials on caries prevention from the National Institute of Dental and Craniofacial Research. Rather than receiving oral hygiene supplies for the entire family over the course of the one-year study period, they will receive oral hygiene supplies once at T1 and only for the child. At T1, parents will be reminded of their obligation to return one year later for the T2 visit at which time the child’s dentition will be again examined and a videotaped tooth brushing observation will be conducted, recommendations made, and the video subsequently analyzed using the TBOS. The only interim contact Control Group parents will have with Program CHWs will be scheduling of their T2 visit.

The schedule of enrollment, intervention and assessment activities is outlined in Table 1 below following the SPIRIT (Standard Protocol Items: Recommendations for Interventional Trials) guidance for clinical trial protocols.

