**Fig. 2 Fig2:**
[figure not shown]
Study schema. This figure presents an overview of study activities and corresponding timeline. The study schema is organized by timepoint: Baseline (T1); 0–6 Months; and 12 Months (T2) post-randomization. The Baseline (T1) timepoint encompasses recruitment, eligibility criteria, enrollment and randomization procedures, and baseline data collection measures. Baseline study activities include both T1 Intervention and Control conditions. The 0–6 Months timeframe represents follow-up activities of the Intervention group condition. Activities represented under the 12 Month (T2) timepoint include final all follow-up data collection measures and activities for both the Intervention and Control group. Intervention and Control Group study activities are described across all timepoints and differences in conditions delineated by arrows depicting flow of study activities

An overview of data to be collected, data sources, and the time points at which they will be collected is presented in Table 2.

**Table 2 Tab2:** Data collection overview

Type	Source	Subjects	Timepoint
Clinical dental examination data	Dental exam charting form	All children screened	T1
		Intervention and Control Group	T1, T2
Tooth brushing observation data	Video recording and TBOS Checklist	Intervention Group	T1, T2
		Control Group	T2
	Tooth brushing duration documented by CHW	Intervention Group	Home Visit
Interview/survey data	Baseline Survey	Intervention and Control Group	T1
	12-month Follow-up Survey	Intervention and Control Group	T2
	Experience Survey	Intervention Group	T2
MySmileBuddy technology data	MySmileBuddy Program App	Intervention Group	T1, T2
CHW implementation and process data	Screening Phase I Form	All parent/child dyads approached for recruitment	T0
	Contact Information Form	All parent/child dyads recruited for dental examination eligibility screening	T0
	Screening Phase II Form	All parent/child dyads presenting to CCPH for dental examination eligibility screening	T1
	Visit Log	Intervention Group	T1, home visit, throughout Intervention period, T2
		Control Group	T1, T2
	Outreach Failure Log	Intervention and Control Group	Throughout study period

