### Comparisons

Logistic regression analysis will compare the odds of having ECC progression between the Intervention and Control Group. The analysis incorporates age and recruitment site to reflect randomization on these variables. If there are any significant Group differences in participant characteristics at baseline, a sensitivity analysis adjusting for potential confounder variables in the regression models will be conducted to help interpret the primary analysis finding. To compare the increase in number of dmft/dfs, we will use a repeated measurements analytic approach.

To model the observed count data, we will use a Poisson mixed model (38, Ch.9) that introduces the number of dmft/dfs and considers these counts to be Poisson distributed conditional upon Gaussian random effects. The model includes indicators for time, Group, recruitment site, age, and Group-by-time. The regression coefficient corresponding to the interaction term is the key parameter of interest for assessing the efficacy of the MSB Program as it represents the post- to pre-treatment ratio of the average rate of dmft/dfs between the Intervention and Control Groups. A random effect is included to account for within-subject correlation and for the possibility of heterogeneity among subjects in the ratio of expected dmft/dfs counts before and after randomization. R packages will be used to fit and carry out inference for the proposed models.

Mediation analysis will be used to test of joint significance of the two paths involving a potential mediator, which was found to achieve the best balance of Type I error and statistical power across the 14 reviewed methods [39]. Potential mediators are risk perception for ECC, self-efficacy for tooth-brushing, skills for tooth brushing, self-efficacy for eating a low cariogenic diet, skills for eating a low cariogenic diet, goal setting reflecting self-regulation processes, physical environmental support, social environmental support, knowledge, positive outcome expectations, and ability to overcome barriers to tooth brushing and adoption of a low-cariogenic diet. This allows for expected partial rather than total mediation, a variable will be declared a mediator if and only if both the test of the regression coefficient of the explanatory factor on the mediator *and* the test of the coefficient of the mediator on the outcome variable are both significant at level alpha = 0.05, two-tailed.

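### Mediators and behaviours share one post-randomisation visit, so the joint-significance rule can often declare a mediator that has no effect on behaviour when the program also moves that variable

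*Protocol article*

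**What the plan says.** The protocol article states the second secondary objective in causal terms: "To assess causal pathways (i.e., mediators and moderators) through which the MSB Program influences twice-daily fluoridated toothpaste use" and a low cariogenic diet (Explanatory objective). Comparisons lists the candidate mediators, among them risk perception, self-efficacy, skills, knowledge, outcome expectations and environmental support. It fixes the decision rule: "a variable will be declared a mediator if and only if both the test" of the explanatory factor on the mediator and the test of the mediator on the outcome are significant at two-tailed 0.05.

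The timing of the data is also fixed:

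- The Abstract (Methods) says that "parents will complete study measures at baseline and 12-months".
- Enrollment describes a "follow up visit at 12 months (T2) when they will again participate in a CHW interview and survey".
- Table 2 gives both arms a baseline survey at T1 and a "12-month Follow-up Survey" at T2, and no other survey of both arms.
- Control group states: "The only interim contact Control Group parents will have with Program CHWs will be scheduling of their T2 visit".
- The one interim behavioural measure in Table 2, "Tooth brushing duration documented by CHW" at the home visit, is for the Intervention Group only. App data are also Intervention only. The brushing video is taken at T1 and T2 in the Intervention Group and at T2 alone in Control.

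**The concern.** Randomisation protects the effect of Group on a determinant and the effect of Group on a behaviour. It does not protect the link from determinant to behaviour. Here that link rests on two quantities recorded at the same visit, about six months after the core intervention ends. A parent who has come to brush twice daily may report more self-efficacy because of it. An unmeasured trait or a change in family circumstances may raise both.

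The rule makes joint significance sufficient, so it leaves no place for time order or for mediator-outcome confounding. The article defends the rule by its balance of Type I error and power among the methods reviewed. That property does not bear on reverse causation or on a common cause. At stake is the explanation of how the program works, which the Background presents as the gap left by earlier studies.

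**Working it through.** **Inputs from the article.** 300 evaluable dyads per group, which is the plan's own figure: 300/(1 − 0.30) = 428.6, so 429 enrolled per group and 858 in total, as stated. Each path is tested at two-sided 0.05. No figure in the article bears on mediators or on brushing rates.

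**Assumed inputs.** Twice-daily brushing Y is 50% in Control and 62% in Intervention. The determinant is M = a·X + δ·Y + noise (SD 1), where X is Group. M has no effect on Y. The second path is adjusted for Group.

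**Approximation by hand.**

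- Within-group variance of Y: (0.50×0.50 + 0.62×0.38)/2 = 0.2428, SD 0.493.
- First path: difference in M = a + 0.12δ; SE = √(1 + 0.2428δ²) × √(2/300), where √(2/300) = 0.0816.
- Second path: r = 0.493δ/√(1 + 0.2428δ²); z ≈ r√597/√(1 − r²).
- Chance of declaring M a mediator ≈ product of the two powers.

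| a (SD) | δ (SD) | First-path z, power | Second-path z, power | Declared |
|---|---|---|---|---|
| 0.3 | 0 | 0.300/0.0816 = 3.67, 96% | 0, 5% | 5% |
| 0.3 | 0.3 | 0.336/0.0825 = 4.07, 98% | r 0.146, z 3.61, 95% | 93% |
| 0.3 | 0.5 | 0.360/0.0841 = 4.28, 99% | r 0.239, z 6.02, 100% | 99% |
| 0 | 0.3 | 0.036/0.0825 = 0.44, 7% | z 3.61, 95% | 7% |
| 0 | 0.5 | 0.060/0.0841 = 0.71, 11% | z 6.02, 100% | 11% |

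**Simulation of the same model, run separately three times.**

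- a = 0.3, no link: 4% to 7%.
- a = 0.3, feedback 0.3 SD: 92% to 95%; feedback 0.5 SD: 99%.
- a = 0.3, shared cause with loading 0.4: 80% to 85%; loading 0.5: 95% to 97%.
- a = 0, feedback 0.3 and 0.5 SD: 7% and 12% (one run).
- a = 0, shared cause: about 5% (same run).

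**A second model.** Continuous variables, 300 per arm, both paths adjusted for baseline (correlation 0.5 with T2), 600 trials per setting:

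- Group moves M and a shared cause exists (residual correlation 0.1 to 0.5): 55% to 100%.
- M only follows from behaviour: 4% to 85%. The rate rises with the program's effect on behaviour (0.2 to 0.5 SD) and with the reverse slope (0.1 to 0.5).
- A shared cause, but Group does not move M: about 3% to 7%.
- Group moves M, no other link: about 5% to 6%.

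So a link between M and behaviour that is not the effect of M can trigger a declaration, but only if Group also shifts M, directly or through behaviour. Otherwise the randomised first path holds the rate near 5%.

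**The case against.** Four points have weight.

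**The first path screens.** A reader might infer that the rule will credit any variable that follows from the behaviour or shares a cause with it. The calculation does not support that: the high rates need the program to move the variable too, or a large program effect on behaviour that feeds back strongly. This stands, and it limits the point. The condition is realistic, however, because Fig. 1 and the description of the Intervention group say that the program targets perceived threat, skills and self-efficacy directly.

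**The article also hedges.** The Abstract speaks of exploring potential pathways, Data management calls the pathways putative, and the close of the Discussion labels the objective exploratory. This lowers the weight of the point. The operative rule still declares mediators, and the objective is still worded as causal.

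**Model details belong in an analysis plan.** Covariates, intervals and sensitivity analyses may well be in one that is not shown, and the article does not say that the second path is unadjusted. Their absence is no fault. But no analysis plan can supply time order that the visit schedule does not collect, and the rule as printed treats joint significance as enough.

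**The sign of the effect.** Two-tailed path tests are conventional, and the coefficients would show an opposing indirect effect. The lack of a sign condition is not an error. Reporting the signed effect is enough.

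**Conclusion.** The point holds in a limited form. For every mediator measured in both arms, the only post-randomisation value comes from the visit that also measures the behaviour, so the second path cannot separate cause from consequence or from a common cause. Under the stated assumptions, a variable with no effect on behaviour is declared a mediator in about 80% to 99% of trials when the program moves it by 0.3 SD and there is feedback or a shared cause. The figure is about 5% to 12% when the program does not move it directly, given 50% versus 62% brushing. The wider range in the second model shows how far the rates depend on the assumed effects.

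Two stronger readings should be avoided. The trial's main result is not in doubt: the primary comparison and the sample size do not depend on this rule. Nor would baseline adjustment alone cure the problem. With 0.3 to 0.5 SD feedback and assumed behaviour persistence of 0.5 to 0.7, such a variable was still declared in 94% to 100% of simulated trials.

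**What to change.** 1. In Comparisons, replace the declaration of a mediator with a statement that the result is consistent with mediation. Align the Explanatory objective, so that no causal pathway is claimed as established from mediators and behaviours both measured at T2.
2. Fit the second path adjusted for Group, T1 mediator, T1 behaviour where it was collected in both arms, age stratum and recruitment site. Control has no T1 brushing video or app data, so measures from those sources cannot be adjusted for in this way.
3. Report the signed indirect effect with a CI and a sensitivity analysis for mediator-outcome confounding.
4. State that reverse causation cannot be excluded.

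The cost is a more modest claim and a little more analysis. No new data are needed, and the article gives recruitment as pending.

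A mediator survey at month 6 should not be presented as enough to keep the causal claim. A month-6 mediator is itself open to month-6 behaviour and to the same shared causes. In simulation with T1 adjustment, false declarations were still 23% to 32% with 0.3 SD feedback and 44% to 68% with 0.5 SD. It would also add a contact to an arm designed to have almost none.

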### Statistical power and data analysis

With power ≥ 80% and 2-tailed alpha = 0.05, a sample size of 300 parent–child dyads per Group is sufficient under various scenarios to detect differences between Control and Intervention Groups (45% vs. 33%, 55% vs. 43%, 65% vs. 53% or 75% vs. 64%) based on a 63.2% one-year caries progression rate among 2–5 year old children treated at the Columbia pediatric dental clinic – a rate consistent with findings from this and other high-risk populations [11, 30, 36, 37]. Accounting for 30% loss to follow up (an estimate higher than experienced in our earlier study), each group will require enrollment of 429 subjects.

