Missing outcome data due to subject dropout can introduce bias that results in misleading inferences since subjects may drop out for reasons related to the outcome of interest. We will use random effect logistic regression models to examine whether missing data are completely random, missing at random, or non-ignorable (38, Ch. 13). In the first two cases our proposed approach based on maximum likelihood estimation is still valid, and multiple imputation of missing outcomes is also valid, as long as the models are correctly specified. If the missingness mechanism is found to be non-ignorable we will use tipping point analysis as sensitivity analysis to assess the potential impact of missingness on our results.

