## Discussion

Over six years of preliminary research [29, 30], an NIDCR-funded planning grant (R34DE023158), and refinement in collaboration with NIDCR (U01DE026739), protocols were developed to minimize recognized large RCT challenges in participant recruitment, enrollment, and retention. Reaching the study’s targeted enrollment is achievable at a pace of 8–9 dyads enrolled weekly over 24 months given that more than 800 age-eligible children visit the recruitment sites each month, at least half of 4–5 year olds and one-quarter of 2–3 year olds in the target population experience ECC, and a preliminary study of 108 families found a 95.6% acceptance rate without financial incentive [30]. While the preliminary study involved only one recruiter 2.5 days/week for five months, this study will engage three CHW recruiters and three support staff five days each week for 24 months and will provide financial incentives. Recruitment and enrollment rates will be monitored weekly and additional resources invested as necessary.

This study encourages retention through financial incentives, user-friendly technology, rapport between CHWs and parents, assistance to families to address social service needs, and an approach that is non-judgmental and encouraging. Initial and semiannual CHW training will help ensure that study protocols are well understood and that appropriate communications and referral skills are established. Adherence to study protocols will be monitored for fidelity by a CHW supervisor and the Study Team through recurrent retraining and bi-weekly meetings that identify and address problems as they arise and weekly review of CHW logs and DCC data for timeliness, completeness, and accuracy (e.g., reported data that are within allowable limits). Corrective action plans will be developed and implemented as needed.

The primary assessment of intervention effects will use an intention-to-treat approach. Implementation data will allow testing of dose–response effects if some subjects do not complete all intervention activities thereby enabling assessment of potential moderating effects attributable to delivery of varying levels of intervention intensity.

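### The tipping-point analysis runs only if dropout is found to be non-ignorable, which the observed data cannot establish; it should be run in every case

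*Protocol article*

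**What the plan says.** The last paragraph under Comparisons accepts that "subjects may drop out for reasons related to the outcome of interest". It then sets out a sequence.

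- Diagnosis: "We will use random effect logistic regression models to examine whether missing data are completely random, missing at random, or non-ignorable".
- If the result is either of the first two: "In the first two cases our proposed approach based on maximum likelihood estimation is still valid". Multiple imputation is called valid as well, provided the models are correctly specified.
- If the result is the third: "If the missingness mechanism is found to be non-ignorable we will use tipping point analysis as sensitivity analysis".

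No analysis that departs from missing at random is stated outside the third branch.

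The primary outcome (Impact objective) is binary: any increase in dmft at 12 months. Comparisons gives it a logistic regression with group, age and recruitment site. The dmft/dfs counts get a Poisson mixed model over both time points. On loss, the power section states "Accounting for 30% loss to follow up (an estimate higher than experienced in our earlier study), each group will require enrollment of 429 subjects". The Discussion adds "The primary assessment of intervention effects will use an intention-to-treat approach".

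**The concern.** Whether dropout is missing at random or non-ignorable depends on how T2 status relates to being seen at T2, given what was observed. For a child who does not return, T2 status is exactly what is missing. There is no intermediate dental examination to give indirect information. A rule that waits for the data to show non-ignorability waits for something they cannot show by themselves.

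A finding of missing at random would end the matter under the stated rule, and the result would not be tested against outcome-related dropout. That dropout is plausible here. Intervention families have health-worker interactions, text messages and quarterly supplies, while Control families' only interim contact with the health workers is the scheduling of T2.

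A second, smaller point is that the reassurance about maximum likelihood is written as if it covered every planned analysis. It fits the Poisson mixed model, where a dropout's baseline count enters the likelihood. It does not automatically carry over to a logistic model of change in dmft, which has no value for a child without T2.

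**Working it through.** **Inputs.** From the power section: 300 evaluable per group, two-sided alpha 0.05, 30% loss, and four Control/Intervention progression pairs. From the Abstract and Table 2: dental outcome at T1 and T2 only.

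**The plan's own figures.** With d the difference, SE0 = √(2·p̄(1−p̄)/300) and SE1 = √(pC(1−pC)/300 + pI(1−pI)/300), power is Φ((d − 1.96·SE0)/SE1). This gives 85.6% (45/33), 83.8% (55/43), 85.0% (65/53) and 83.5% (75/64), all at least 80% as stated. Enrolment is 300/0.70 = 429 per group, 858 in total. The sample size reproduces, and 429 − 300 = 129 per arm may lack T2.

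**Can the data choose between the mechanisms?** Suppose 53% of 300 observed Intervention children progress (159 children). The full-arm rate is (159 + 129·q)/429, where q is the unseen rate among dropouts. Compare it with a Control rate of 65%.

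| q in the 129 missing | Full-arm rate | Effect (points) |
|---|---|---|
| 33% | 47% | 18 |
| 53% | 53% | 12 |
| 73% | 59% | 6 |
| 93% | 65% | 0 |

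All four rows share the same observed data. In this simple case without covariates only the second is missing at random, and no fit to the observed children can select it.

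**How much departure matters?** Leave Control dropouts at the Control completer rate and raise Intervention dropouts by a fixed shift δ. The estimate becomes d − (129/429)·δ. With δ fixed, the standard error stays at SE1. Significance is lost at δ = (d − 1.96·SE1)/(129/429).

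For 65/53: SE1 = √(0.2275/300 + 0.2491/300) = 0.0399. The completer estimate is 12.0 points (95% CI 4.2 to 19.8), and δ = (0.12 − 0.0781)/0.3007 = 0.139.

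| Control/Intervention | δ at loss of significance | Rate in Intervention dropouts |
|---|---|---|
| 45/33 | 14.1 points | 47.1% |
| 55/43 | 13.5 points | 56.5% |
| 65/53 | 13.9 points | 66.9% |
| 75/64 | 12.3 points | 76.3% |

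At 65/53 the effect reaches zero at δ = 0.12/0.3007, about 40 points (a rate of about 93%). The extreme-case bounds are 0.12·(300/429) ∓ 129/429, or −21.7 to +38.5 points.

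**If loss is lower.** At 20% loss (343 seen, 86 missing per arm), SE1 = √(0.4766/343) = 0.0373 and δ = (0.12 − 0.0731)/(86/429) = 0.234, about 23 points. At 10% (386 seen, 43 missing), SE1 = 0.0351 and δ = (0.12 − 0.0689)/(43/429) = 0.51. That would need a rate above 100%, so this departure alone could not overturn significance.

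**The maximum-likelihood statement.** Assume no true effect, two equal baseline-dmft strata progressing at 45% and 81% (63% overall), and 30% loss in each arm. Let Intervention dropout be 20%/40% across the strata. Intervention completers then progress at (0.5·0.8·0.45 + 0.5·0.6·0.81)/0.7 = 60.4%. The spurious difference depends on Control dropout:

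- 20%/40%: Control completers also 60.4%, difference 0.
- 25%/35%: (0.5·0.75·0.45 + 0.5·0.65·0.81)/0.7 = 61.7%, difference 1.3 points.
- 30%/30%: 63.0%, difference 2.6 points.

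The strata are assumptions, not figures from the article. They show that a completer analysis without baseline dmft can be biased under missing at random when dropout relates to baseline dmft differently by arm, and is not biased in this null example when the relation is the same.

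**The case against.** Several points on the other side stand. The 30% is a planning allowance that the article calls higher than earlier experience. Both arms are offered $100 for completing T2, and outreach failures are logged in both, so differential loss is plausible rather than shown. The rule governs a sensitivity analysis and leaves the primary estimate unchanged. A joint model of outcome and dropout can return a classification, so the trigger could fire; but its answer would come from the model's assumptions. The SAP may add analyses, but the article states the conditional rule itself, so this is more than missing detail.

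A reader might go further in four ways that the article does not support.

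- *The primary analysis is complete-case and so not intention-to-treat.* The article never says complete-case. It names multiple imputation as valid and states intention-to-treat. How the binary outcome is handled may be left to the SAP.
- *The random effect in the dropout model is not identified.* The specification is not shown; the effect could be for clusters or shared with the outcome model.
- *Any dropout related to baseline dmft biases the comparison.* With the same relation in both arms the null example above shows none.
- *Non-ignorable dropout always biases the result.* If 60% of progressors and 80% of non-progressors return in both arms, the completer odds ratio for 65/53 is (0.53·0.6/(0.47·0.8)) / (0.65·0.6/(0.35·0.8)) = 0.607, the same as in full data.

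Multiple imputation, as the article describes it, also rests on missing at random. It does not replace the tipping-point analysis.

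**Conclusion.** The point holds and should be fixed. The stated trigger asks the data to separate missing at random from non-ignorable, which one post-baseline examination cannot do without untestable assumptions. Outcome-related dropout **may** therefore go unexamined; it does not follow that it will, or that the primary result is biased.

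The size at the planning rates is a tipping shift of about 12 to 14 points in Intervention dropouts. This assumes 30% loss in each arm, completer rates equal to the planning rates, Control dropouts like Control completers, a fixed shift and no covariate adjustment. Lower loss makes the result sturdier.

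The statement on maximum likelihood is too broad as worded, but its consequence for the logistic model depends on arm-specific dropout by baseline dmft. The article gives no figures from which to size that, so no type I error is claimed.

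**What to change.** 1. Remove the classification of the missingness mechanism as a decision rule. Keep the dropout models as a description of who was lost, by arm, age, site and baseline dmft.
2. Run the tipping-point analysis of the primary binary outcome in all cases, with the dropout shift varied separately in each arm.
3. Limit the statement that maximum likelihood stays valid under missing at random to the Poisson mixed model. For the logistic analysis of progression, add multiple imputation by arm that includes baseline dmft. This adds an analysis and need not replace the primary one.

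The cost is protocol and SAP wording and modest programming. No new data are needed, and enrolment stays at 429 per group (858). The article's registration table lists recruitment as pending, so the change can be made before any outcome is seen.
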